### 5.1.1 Known Adverse Events

In the previous monocenter trial of Deprexis in MS, we considered new occurrence of suicidal ideation or intent as well as worsening of depressive symptoms above the clinical threshold as potential adverse events. None of the enrolled participants met the predefined criterion for acute risk of suicide (response 3a or 3b on SBQ-R item 3 plus score of 5 or 6 on SBQ-R item 4) at baseline or the after the intervention. For the low threshold definition using BDI item 9, the criterion was not met by any patient in the Deprexis group (pre: n=0; post: n=0) but in one instance in the WLC group (pre: n=1; post: n=1). For SBQ-R item 4, n=2 patients met the low threshold criterion before and n=0 patients after Deprexis in the treatment group. In the WLC group, this criterion was met in n=4 at baseline and n=3 nine weeks after baseline. However, no evidence for new occurrence of suicidal ideation was seen during the trial in either of the groups using the low threshold criteria. Worsening of depressive symptoms during the trial from below to above the cut-off for “caseness” (BDI > 13) was observed in n=3 patient in the WLC but not in the Deprexis group.

### 5.1.2 Treatment Plan

[figure not shown]

Figure 1: Trial Design Schematic and Treatment Plan.

### **5.1.3 Compliance**

#### Ascertainment of compliance

We will assess time spent working with the Deprexis program by each patient as a measure of treatment adherence. The Deprexis interface tracks usage time of each participant, thereby allowing evaluation of treatment adherence. The usage log of Deprexis uses 5-minute blocks and excludes each block of inactivity so that the logged usage times is a good estimate of time spent working with the program. We will use the time spent working with the program and the number of modules completed (with at least 15 minutes spent in the module) as an indicator of treatment adherence. For DeprexisPlus, we will also collect data on number of email contacts per patients and total time spent on each email.

### **5.2 Emergencies**

In case of emergency supposedly due to application of IMP treatment is immediately discontinued. Regulatory reporting duties apply. As we consider occurrence of suicidal ideation and intent as a potential adverse event in patients with depressive symptoms, we have developed specific SOPs for responding to such events (see SOP suicidality in the appendix).

## 6 Trial Conduction

### 6.1 Screening and Recruitment

Screening will happen within the participating centers.

Recruitment

- Recruitment happens as a distinct informational visit.

### 6.2 Informed Consent

Patients will be informed about the conduction of the trial in a personal conversation by a physician. They will receive the written patient information, and be given time to read it thoroughly and without haste. If further questions arise, the physician will answer them openly and correctly. If the patient is able to consent, but unable to sign the documents, an independent witness may sign the forms to document the orally given consent by the patient.

### 6.3 Prevention of simultaneous inclusion in multiple trials

Inclusion in another interventional trial is an exclusion criterion. It is the duty of the recruiting investigator to rule out current participation in another trial. Patient information will explicitly state the impossibility to partake if already participating in another trial.

### 6.4 Enrolment

- Recruitment of new patients at any of the study sites will be tracked in pseudonymized form by the study platform

### 6.5 Visits, Investigations and deviations of standard-of-care

#### Methodological Continuity

Same methods to measure variables and outcome parameters will be used throughout the conduction of the trial.

#### Time points

Treatment will be administered for 12 weeks during the primary trial phase.

#### Complementary Scientific Program

Several ancillary studies are planned, some of them only in selected sites:

**Neuroimaging:** Structural and functional (resting state and emotion regulation task) MRI studies are planned at several sites. These will be conducted only during the clinical visits (V1 and V2).

**Psychological moderators and predictors of treatment response:** Additional paper and pencil questionnaire to measure potential psychological moderators and treatment response predictors will be obtained at several sites. These will be conducted only during the clinical visits (V1 and V2).

**Molecular and cellular shifts in the immune system:** Obtaining blood samples for storage of serum, plasma and cryopreserved peripheral blood mononuclear cells (PBMCs) are planned at several sites. These materials will be used to explore potential immunological markers of treatment response. Blood samples will be obtained only during the clinical visits (V1 and V2).

| Investigation                | V1
(wk 0) | Interim
(wk 4) | Interim
(wk 8) | V2
(wk 12) | V3 Follow-up
(M 6) | V4 Follow-up
(M 12) |
|------------------------------|--------------|-------------------|-------------------|---------------|-----------------------|------------------------|
| Check for selection criteria | X            |                   |                   |               |                       |                        |
| Informed Consent             | X            |                   |                   |               |                       |                        |
| Case history                 | X            |                   |                   |               |                       |                        |
| Clinical Examination         | X            |                   |                   | X             |                       |                        |
| Questionnaires               | X            | X                 | X                 | X             | X                     | X                      |
| Demographic data             | X            |                   |                   |               |                       |                        |
| Laboratory examination       |              |                   |                   |               |                       |                        |
| Blood sampling (optional)    | X            |                   |                   | X             |                       |                        |
| MRI (optional)               | X            |                   |                   | X             |                       |                        |
| Incidence of AEs/SAEs        |              | X                 | X                 | X             | X                     | X                      |

**Blue:** Clinical visits at the study site; **Black:** Online assessments

In case of a loss to follow up we contact the local registration authorities to ensure we can reach the highest amount of patients possible, even if they moved.

#### 6.5.1 V1 (clinical visit)

Informed consent is obtained and selection criteria will be checked. If all inclusion criteria are met and all exclusion criteria are excluded baseline examination will be performed and patients will be randomized.

The following data will be collected:

- Case history and demographic data
- Clinical examination, including
  - a basic medical examination
  - a neurological examination
  - a structured clinical interview for psychiatric symptoms
  - self-report questionnaires
- *Laboratory examination (optional)*
  - Immunology
- *Neuroimaging (optional)*
  - Structural MRI
  - Resting-state fMRI
  - Task fMRI

#### 6.5.2 V2 (clinical visit) at 12 weeks post randomization (+/- 7 days permissible)

Visits will be conducted on site at unit/neurological ward:

- Clinical examination, including
  - a basic medical examination
  - a neurological examination
  - a structured clinical interview for psychiatric symptoms
  - self-report questionnaires
- Incidence of AEs
- *Laboratory examination (optional)*
  - Immunology
- *Neuroimaging (optional)*
  - Structural MRI
  - Resting-state fMRI
  - Task fMRI

### 6.5.3 Follow-Up assessments – V3 and V4 (online) (+ 28 days permissible)

Follow-up assessments will be conducted online. The following data will be collected at V3 and V4:

- Self report questionnaires
- Incidence of AEs

### 6.5.4 Laboratory Details

No routine laboratory markers will be obtained. In some centers, ancillary scientific studies are carried out to study immunological correlates of depressive symptoms in MS and their response to treatment using serum samples and PBMCs (see above)

## 6.6 Duration of trial participation for the individual subject

Prerequisites of trial completion for the individual subject

- Duration of treatment: 12 weeks
- Duration of follow-up: 1 year after study inclusion

## 7 Risk-Benefit-Consideration

### Risks, Adverse Reactions, Burden, Advantages and Disadvantages for Participants

#### RISKS

**Risk of the treatment:** The intervention is generally considered low risk as Deprexis has been used in numerous clinical trials without evidence for adverse events and is categorized as a “low risk” medical device according to its German CE®-certification. The FDA has reviewed Deprexis in July 2015 and classified it as a mobile medical application. The FDA does not intend to enforce any regulatory requirements under applicable provisions of the Federal Food Drug and Cosmetic Act, Section 513(g). A potential safety concern regarding an online intervention targeted at depression is suicidal ideation and intent.

*Procedures implemented to control risk:* Acute risk for suicide at baseline (as determined by the SBQ-R, see above) will lead to exclusion from the trial and patients will immediately be referred to specialists for crisis intervention. In our previous trial (26) we found no evidence for the new occurrence of suicidal thoughts during the trial or at 6-months follow-up in the Deprexis or waitlist control group. Similarly, previous trials of Deprexis (including the recent trial of patients with severe depression (23)) also showed no evidence for increased suicidal ideation and intent. However, in the proposed trial we will establish a detailed protocol for detection and response to suicide risk. During the clinical visits, all patients will be asked about suicidal ideation and intent. In addition, we will obtain information about emergency contacts (friends/family) in a standardized manner. If participants express suicidality during their clinical visit, the site PI (neurologist or experienced clinical psychologist) will be contacted immediately by the study coordinator and will explore things further with them in person. If participants appear to present an immediate danger to themselves, then standard procedures established at each site will be followed for possible commitment. Participants will be informed in the informed consent form about the possibility that confidentiality may need to be breached if they express an immediate, serious danger to themselves. Finally, the secure online study platform will include a feature where helpline numbers will be automatically displayed if response on the BDI-II indicates suicide risk at any time (item 9 = 3). In this case, an automated email alert will also be sent to the study center of the patient for a follow-up phone call by the study coordinator and the site PI (neurologist or experienced clinical psychologist).

**Risk of blood sampling:** Blood sampling is considered low risk. Blood drawing from a vein may cause pain from insertion of the needle, light headedness, faintness, bruising, localized bleeding which may

look and feel like a bruise, and rarely inflammation of the vein, clotting of the vein and/or infection at the needle site.

*Procedures implemented to control risk:* Blood sampling will be conducted according to established protocols and performed by authorized personnel (study nurse or physician).

**Risk of MRI examinations:** There are no specific side effects from having an MRI scan, although some patients become claustrophobic (fear of enclosed space) during the MRI scan. Because the MRI uses magnets, participants with cardiac pacemakers, certain artificial heart valves, and/or other metallic/electronic material in their bodies cannot undergo MRI imaging and will not be eligible for this study. MRI is painless and requires only that you lie in the scanning machine. The machine produces loud sounds. It is therefore essential that you wear earplugs during the MRI scan to protect your hearing. Patients with severe claustrophobia during prior MRI scans or patients with a prior allergic reaction to gadolinium should not participate in this study.

*Procedures implemented to control risk:* Patients will carefully be examined for potential contraindications for MRI scans and scans performed by authorized personnel under appropriate supervision of a neuroradiologist.

## **BURDEN**

The main burden for participants in the trial is coming in for the clinical examinations (V1 and V2), completing the online questionnaires and working with the Deprexis program. Patient will be reimbursed for their time and effort.

## **ADVANTAGES**

Participants will receive a novel online program to reduce depressive symptoms free of charge, either immediately or after waiting for 6 months (i.e. all patients will receive treatment). Participants may also benefit from a thorough clinical and psychological examination conducted at V1 and V2 by authorized personnel under the supervision of experienced clinicians.

# **8 Discontinuation and Ongoing Treatment**

## **8.1 Premature discontinuation of participation for an individual subject**

### Reasons to discontinue participation (Criteria of discontinuation)

The following conditions are obligatory reasons to discontinue further participation in the trial according to the protocol:

- Decision of the patient
- Any further situation rendering further participation potentially harmful to the patient at the discretion of the investigator

The following conditions are possible reasons to discontinue further participation in the trial according to the protocol, and have to be reviewed as soon as possible by the principal investigator:

- Serious adverse event (SAE) and Suspected unexpected serious adverse reaction (SUSAR)
- Retrospectively assessed exclusion criterion

## **8.2 Premature discontinuation of the trial**

A premature discontinuation of the trial may be decided if new scientific data emerging during the course of the trial changes the risk-benefit-balance significantly. If such data emerges, recruitment and treatment of currently treated patients will be paused immediately. A final decision on continuation or termination of the trial will then be made by the principal investigator.

SAEs will be assessed in detail at the second clinical visit for each patient with a specific focus on new occurrence of psychopathology and suicidal ideation and intent (based on MINI structured interview and the SBQ-R at the M3 clinical visit). There are no predefined stopping rules.

### 8.3 Ongoing procedures besides the protocol

#### After premature discontinuation of the trial

Patients will be followed up at the same time points as lined out in the regular study protocol for safety endpoints if they agree to.

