## **2.7 Timing of Outcome Assessments**

Outcomes are measured at week 0 (baseline) and week 12 when visiting the clinic. In addition, BDI-II outcomes are measured at week 4 and 8 in online assessments. Follow-up visits for all patients who want to use MSDeprexis after 6 and 12 month are conducted online.

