| Safety                                                                                | Documentation of adverse events with every visit.
SOP suicidality                                                                                                                                                                                                                                                                                                                                                                                                                                                                                                                                                                                                                                                      |
| Criteria for Discontinuation                                                          | 
Of Participation for an Individual:
Obligatory: Personal decision of the individual, potential harm (occurrence of clinically relevant suicidal ideation or at the discretion of the investigator)
Possible: Retrospectively assessed exclusion criterion
Severe Adverse Event (SAE) or Suspected Unexpected Serious Adverse Reaction (SUSAR)
 
Of the trial itself:
Change of the risk-benefit-analysis
                                                                                                                                                                                                                                                                        |
| Statistical Evaluation/Sample Size Calculation                                        | The primary outcome change in BDI from baseline to week 12 will be analyzed as intention-to-treat (ITT) by means of linear mixed effect models for repeated measures adjusted for baseline measurements including all patients with at least one post-baseline measurement. A sample size of 100 patients per intervention group gives a conjunctive power (probability of rejecting both null hypotheses comparing Deprexis and DeprexisPlus to waitlist control) of 90% for a Dunnett test at the usual one-sided significance level of 2.5%. Adjusting for 20% dropout we aim to recruit 125 patients per group resulting in a total sample size of 375 patients.                                                      |

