### 12.5.1 Hypotheses

**Primary hypothesis:** All analyses will be conducted as intention-to-treat (ITT). To definitively test the effectiveness of Deprexis for reducing depressive symptoms in MS at the end of treatment, the primary outcome change in BDI from baseline to week 12 will be analyzed by means of linear mixed effect models for repeated measures adjusted for baseline measurements with fixed effects for intervention, center, time and baseline BDI score, and random subject effects for individual patients including all patients with at least one post-baseline measurement (29). Least squares means will be reported for the intervention groups with 95% confidence interval (CI) as well as the difference between the least squares group means with 95% CI. Deprexis vs. WLC and DeprexisPlus vs. WLC will be tested by a Dunnett test controlling the familywise type I error rate at the level of 2.5%

(one-sided). *The primary hypothesis will be tested in a confirmatory manner.* In a secondary step, we will determine the added value of therapist email support Deprexis vs. DeprexisPlus at a two-sided level of 5%, if efficacy of Deprexis and DeprexisPlus for reducing depressive symptoms in MS could be demonstrated.

**Secondary hypotheses:** The analyses of secondary and tertiary endpoints (such as BDI-FS, QoL, cognitive function and fatigue scales) will follow the same approach as the analyses described for the primary endpoint. The proposed trial will create a large data set from n=400 MS patients and followed for 12 months that will enable us to gain valuable insight into the potential predictors, confounders, intermediates in the causal pathway, and interactions of Deprexis(Plus) treatment effects. In supporting exploratory analyses we will investigate potential moderators of treatment effects by including these and their interaction with treatment in the linear mixed effects models described above. Potential moderators include disease-modifying therapies (DMTs), level of disability at baseline (as measured by Disease Steps and patient-rated EDSS), cognitive status at baseline (as measured by BICAMS), and level of fatigue at baseline (as measured by the FSMC).

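### No passage secures the week-12 BDI-II from patients discontinued under protocol 8.1, so for them the intention-to-treat contrast rests on modelling rather than on observed outcomes

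*Supplement*

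**What the plan says.** Protocol 8.1 lists "obligatory reasons to discontinue further participation in the trial according to the protocol" (the patient's own decision, or potential harm as judged by the investigator). It then lists possible reasons, among them an SAE. All of them end participation. None is described as ending only the use of the programme.

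Protocol 8.3, under a heading about premature discontinuation of the trial, keeps patients in follow-up at the time points set out "in the regular study protocol for safety endpoints if they agree to". The preceding section, 8.2, uses the same phrase for closing the study as a whole: "A premature discontinuation of the trial may be decided if new scientific data emerging during the course of the trial".

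Protocol 12.5.1 states: "All analyses will be conducted as intention-to-treat (ITT"; 12.5.2 repeats this. SAP 3.3 and 5.2 analyse all randomised patients with at least one post-baseline measurement in a repeated-measures mixed model, with LOCF and multiple imputation as sensitivity analyses.

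On how the primary scale is collected, SAP 2.7 says: "Outcomes are measured at week 0 (baseline) and week 12 when visiting the clinic". It places the week-4 and week-8 BDI-II online. Protocol 6.5.2 also puts the week-12 visit on site.

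On suicidal ideation, the synopsis lists among its obligatory reasons "potential harm (occurrence of clinically relevant suicidal ideation or at the discretion of the investigator". Section 8.1 does not name it. Section 9.1 makes it an SAE criterion, and 8.1 treats an SAE as only a possible reason.

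**The concern.** An intention-to-treat contrast needs the outcome of patients who come off treatment as well as of those who continue. Here a patient can be taken out because continuing is judged harmful or because of an SAE. One SAE criterion is a score of 3 on item 9 of the BDI-II, so removal can depend on the primary instrument itself. These patients may well fare worse than those who stay.

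If their week-12 score is not sought, the mixed model predicts it from patients in the same arm with similar baseline and earlier scores. A patient who leaves before week 4 has no post-baseline value and drops out of the primary model altogether. The estimate then moves toward the effect that would be seen if nobody had discontinued. The BDI-II is already on the study platform, so this loss could be avoided.

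**Working it through.** **1. The plan's own figures.** Inputs from SAP 2.3 and the protocol's sample size estimation: 100 evaluable patients per arm, standardised differences 0.5 and 0.8, Dunnett test at one-sided 2.5%, 20% dropout.
- Dropout: 100 / (1 − 0.20) = 125 per arm; 3 × 125 = 375. This matches.
- Conjunctive power, simulated for a single-step Dunnett test (shared control, correlation 0.5, 297 degrees of freedom, critical value 2.220, 2,000,000 replicates): 90.5%, against 90% stated. This matches.

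The sample size is sound on its own terms. It shows only that 125 − 100 = 25 patients per arm, 75 in all, are budgeted without evaluable primary data. The phase II trial cited in the protocol lost 10/45 = 22.2% and 9/45 = 20%, so 20% is a realistic figure.

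**2. The two readings of 8.3.**

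| Reading | Follow-up of a discontinued individual | Week-12 BDI-II secured? |
|---|---|---|
| 8.3 covers individuals | Regular time points, safety endpoints, if the patient agrees | Not expressly: both documents list the SBQ-R as the safety measure and the BDI-II as the primary endpoint |
| 8.3 covers only closure of the whole trial | None stated | No |

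The gap does not depend on which reading is right.

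**3. Size.** Assumptions, not in the documents: a share q of the active arm discontinues and keeps a fraction f of the effect; the effect in those who stay is 0.50 SD (the plan gives 0.5 as its overall assumption, not as an effect among stayers); dropout in the waitlist arm is uninformative. Then

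true effect = (1 − q) × 0.50 + q × f × 0.50,

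and a model that treats discontinuers like stayers returns up to 0.50.
- q = 0.20, f = 0: 0.80 × 0.50 = 0.40; overstatement up to 0.10 SD.
- q = 0.20, f = 0.5: 0.40 + 0.20 × 0.25 = 0.45; up to 0.05 SD.
- q = 0.10, f = 0: 0.45; up to 0.05 SD.
- q = 0.10, f = 0.5: 0.45 + 0.10 × 0.25 = 0.475; up to 0.025 SD.

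The q = 0.10 lines show the case in which half of the dropout is withdrawn consent or loss to follow-up. The figures scale with the effect: for the guided arm at 0.80 SD and q = 0.20, the true effects are 0.64 (f = 0) and 0.72 (f = 0.5).

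**4. Power if the scores are collected.** With all 125 per arm observed and q = 0.20, conjunctive power by the same simulation is about 96% (f = 1), 91% (f = 0.5) and 83% (f = 0). Observing all 125 is the best case, since some patients will withdraw consent.

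**5. Suicidal ideation.** Synopsis: obligatory reason. Section 8.1 read with 9.1: not listed as obligatory, and only a possible reason by way of the SAE definition. The investigator's discretion in 8.1 could reach the same outcome in a given case, but it does not make the two rules the same.

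**The case against.** A reader might infer that stopping the programme means leaving the trial, so that everyone who stops yields no week-12 BDI-II and the intention-to-treat question goes unanswered. The documents do not support that.

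- Low or absent use is recorded as adherence (SAP 3.2, protocol 5.1.3). In the guided arm, inactivity prompts an offer of help (protocol 5.1). Protocol 5.2 speaks of stopping treatment without saying that participation ends. SAP 3.3 makes patients who registered in the programme a separate sensitivity set, which implies that non-registrants belong in the main one.
- The heading of 8.3 echoes 8.2, so applying it to individuals is an inference.
- BDI-II item 9 is an SAE trigger at any assessment, and worsening of depressive symptoms counts as a potential adverse event (SAP 5.4). Safety follow-up could therefore include the BDI-II.
- Nothing bars online completion at week 12. SAP 5.3 shows that the baseline assessment was itself online.
- Week-4 and week-8 scores enter the model, LOCF and multiple imputation are planned, and patients lost to follow-up are traced (protocol 6.5).

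All of this stands, and it limits the point to patients discontinued under 8.1. It does not close the gap. That safety follow-up could include the BDI-II is not a commitment to collect the total score. LOCF and multiple imputation replace an outcome that could have been asked for. Protocol 12.5.2 also foresees models for informative dropout if missing data are substantial, but the SAP specifies none.

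**Conclusion.** The point holds in limited form. For patients discontinued under 8.1, no passage secures the primary outcome, and their part of the intention-to-treat contrast rests on untested missing-data assumptions. The question is answered under assumptions, not left unanswered.

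For a 0.50 SD effect the overstatement is at most 0.05 to 0.10 SD. That bound takes the whole 20% as discontinuers who could have been followed, lets them keep half or none of the effect, and gives no credit for earlier scores. The documents do not say what share of dropout is of this kind, so the real figure is smaller by an unknown amount. The change is worth making because the loss can be informative and is cheap to prevent.

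The contradiction on suicidal ideation is real but separate, and it adds nothing to the size above.

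**What to change.** In protocol 8.1 and 8.3, distinguish stopping the programme from withdrawing consent to follow-up, and say whether 8.3 applies to individuals, to closure of the trial, or to both. State that every randomised patient who has not withdrawn that consent is asked for the BDI-II at weeks 4, 8 and 12 through the existing platform, with online completion at week 12 if the clinic visit is missed. State in the SAP that these values enter the primary analysis. For scores still missing, the SAP could take up the informative-dropout models already named in protocol 12.5.2.

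The cost is wording and use of a questionnaire that already exists, with no added visits. The downside is that a few week-12 scores would be completed at home rather than in the clinic.

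Separately, the synopsis, 8.1 and the SAE definition in 9.1 must be reconciled on whether suicidal ideation is an obligatory or a possible reason to discontinue. Which rule applies is for the investigators to settle.
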